
Accordingly, *the research hypothesis* is the following. Given the mentioned above social-cultural features of the Kazakh’s way of life, the obtained frequencies of different IEM are expected to be lower than in other countries practicing historically approved consanguineous marriages. Thus, *the study goal* is to perform selective screening for hereditary metabolic diseases among patients aged from 1 day to 18 years in western Kazakhstan using the LC-MS/MS method, with establishing the reference values for the content of amino acids, acylcarnitines, and succinylacetone in blood samples of healthy children.

Tasks:1. To assess the burden of metabolic disorders detected by LC-MS/MS in western Kazakhstan by examination of children at clinical risk in pediatric clinics throughout the region;2. To set the reference values of metabolites in the child population;3. To analyze the age distribution, prevalence, and age of onset for each identified IEM, further comparing the obtained findings with those from previously published reports in other populations.

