### 2.2 Selection of subjects

#### 2.2.1 Sample size estimation

When calculating the sample size for the upcoming project on selective screening, we relied on published similar studies. Researchers pointed out the following essential factors contributing to the sample size calculation: Daniel’s formula for prevalence studies in case of expanded screenings, the reported frequencies of different IEM within the studied populations, and the number of infants born in the country during the period of interest (Yoon et al., 2005; Golbahar et al., 2013; Hassan et al., 2016; Shibata et al., 2018; Sarker et al., 2019; Manta-Vogli et al., 2020). Notably, many researchers corrected their calculations, considering the situation with consanguineous marriages in their country.

According to the review by Shibata N et al., the IEM overall detection frequency was 3.0% (1.2% in Japan and 9.2% in other Asian countries) (Shibata et al., 2018). Yoon et al. reported 5.4% IEM among South Korean annual births (Yoon et al., 2005). Of these data on IEM frequency throughout Asian countries, Mongolian values (1.6%) have attracted our attention due to the similar nomadic history and way of life where consanguineous marriages were strictly forbidden (Shibata et al., 2018). Along with that, the Mongolian index does not include all types of IEM except the most distributed.

Based on mentioned factors, we requested data on the number of childbirths across the four provinces (oblasts) of western Kazakhstan within 3 years before the project started. The average rate of infants born alive annually ranged between 69–73,000 (https://stat.gov.kz/en/industries/social-statistics/demography/publications/). Thus, we have decided to build on the IEM average frequency of 2%–2.5% and determined the expected sample size of 1,500 children for selective screening with 750 healthy controls.

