### 3.4 Presenting IEM frequencies in the child population

The frequency of inborn errors of metabolism detected using tandem mass spectrometry, depending on the geographical location and type of IEM in western Kazakhstan during the period from 2023 to 2024, can be represented graphically in the form of accumulation diagrams demonstrating the contribution of AAD, OA, and FAOD to the total incidence of IEM. Also, these data can be presented in the form of a table. The data will include the total number of IEM cases in the high-risk group of children and the absolute number and frequency of cases for each identified disease. Detection rates for selective screening and incidence will be calculated according to the number of children born in western Kazakhstan during the study period, in 2023–2024, for each specific disease. These data will allow for estimating the number of affected male and female children and determining which IEMs were the most common in the studied population. Given that selective screening of the child population in western Kazakhstan will be carried out for about 2 years (2023–2024, recruitment of high-risk children), the incidence rate for each class of disorders (AAD, OA, FAOD) will be established, taking into account the total number of births each year.

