## 4 Discussion

The present study assumes only selective screening for IEM. Implementing ENBS, which allows for thoroughly assessing the prevalence of IEM in the child population of western Kazakhstan, is currently unavailable due to a lack of proper financing. In addition, given that the overall prevalence of IEM in populations is relatively low, less than 1:100,000 for most of them, coverage for expanded newborn screening should be total. Besides, it is known that not all IEMs are diagnosed during ENBS, as some disorders debut at a later age (Hassan et al., 2016). Nonetheless, the data of selective screening conducted among children at high risk of IEM, given the inclusion in the study of the largest pediatric hospitals in western Kazakhstan, can serve as a basis for calculating the relative frequencies of various IEMs in the child population of the region.

Detection rates for selective screening and incidence will be calculated according to the number of children born alive in the region during the study period, in 2023–2024, for each specific disease. These data will allow for estimating the number of affected male and female children and determining which IEMs are the most common. The frequencies of each IEM revealed across the child population of western Kazakhstan will be matched with incidence data in other regions of the world.

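### Frequencies are to be compared disorder by disorder, and only for disorders found, although the sample yields about one expected case per disorder

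*Protocol article*

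**What the plan says.** The Introduction of the protocol article states one research hypothesis: "the obtained frequencies of different IEM are expected to be lower than in other countries" where marriage between relatives is an accepted custom. Task 3 is to analyse "prevalence, and age of onset for each identified IEM, further comparing the obtained findings with those from previously published reports in other populations". Section 3.4 will report "the absolute number and frequency of cases for each identified disease", and the Discussion adds: "The frequencies of each IEM revealed across the child population of western Kazakhstan will be matched with incidence data" from other parts of the world. In all three places the unit is the single disorder, and only one with at least one case.

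Section 2.2.1 bases the sample on an overall frequency of 2–2.5% for all disorders together and "determined the expected sample size of 1,500 children for selective screening with 750 healthy controls". No per-disorder frequency enters that reasoning. Section 2.3.5 says that the frequency of 37 disorders will be assessed, and Table 3 lists 12 + 14 + 11 = 37. Section 3.4 also promises the total number of cases and an incidence rate for each of the three classes: amino acid disorders (AAD), organic acidemias (OA) and fatty acid oxidation disorders (FAOD).

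**The concern.** The hypothesis is put at a level for which the sample was not sized. With about one expected case per disorder, the observed frequency is in practice 0, 1 or 2 in 1,500, and its position relative to a published figure is governed largely by chance.

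The restriction to disorders found adds a bias of its own. A disorder with no case is the one most likely to look rarer than elsewhere, and it leaves the comparison. Those that stay had at least one case, so their observed frequencies are too high on average.

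Two things are at stake. The study could misjudge its only hypothesis in either direction for single disorders. The Discussion also makes the choice of disorders for a future national newborn panel depend partly on the frequencies found here, so upward-biased frequencies and omitted zeros could colour that choice.

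**Working it through.** **Inputs.** Children screened: 1,500 (section 2.2.1). Overall frequency: 2–2.5% (section 2.2.1). Disorders: 37 (section 2.3.5, Table 3). Outside overall frequencies: 3.0%, of which 1.2% in Japan and 9.2% in other Asian countries (section 2.2.1). Births: 69,000–73,000 a year (section 2.2.1). The spread of cases over disorders is not given, so averages are used and other spreads are shown as assumptions.

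**The plan's own figure.** The 1,500 cannot be re-derived, because no precision is stated. With the usual prevalence formula n = 1.96² p(1−p)/d², 1,500 implies d = 0.71 percentage points at p = 2% and 0.79 at p = 2.5%. That is a sensible precision for the overall rate.

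**Expected cases.**
- Total: 1,500 × 0.02 = 30; 1,500 × 0.025 = 37.5.
- Per disorder: 30/37 = 0.81; 37.5/37 = 1.01.
- Average rate per disorder: 2%/37 = 0.054%; 2.5%/37 = 0.068%.

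**What a single disorder can show** (exact Clopper-Pearson 95% limits).
- 0/1,500: upper limit 0.246%, which is 3.6–4.5 times the average planned rate (0.246/0.068 to 0.246/0.054).
- 1/1,500: 0.002–0.371%, the upper limit being 5.5–6.9 times that rate.
- The average comparator rate at 9.2% is 9.2%/37 = 0.249%. Zero cases just excludes it (0.246%); one case does not (0.371%). At that rate the only count that supports a claim of lower frequency is zero, which is the count that the identified-only wording removes.

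**Bias from dropping zeros.** For a Poisson count with mean λ, the mean given at least one case is λ/(1 − e^−λ), an inflation of 1/(1 − e^−λ).

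| λ | e^−λ | Inflation |
|---|---|---|
| 1.01 | 0.363 | 1.57 |
| 0.81 | 0.444 | 1.80 |
| 0.30 | 0.741 | 3.86 |

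**How often a raw value would fall below the comparator.** This depends on assumptions that the document does not settle. Truth is 30–37.5 cases; the spread is even or by power laws with exponents 0.5–1.5.

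| Comparator | All 37 disorders | Disorders with a case |
|---|---|---|
| Same rate, even spread | 44% (at 2%), 73% (at 2.5%) | 0% (at 2%), 58% (at 2.5%) |
| Same rate, power laws | 53–79% | 13–25% |
| 9.2%, any of these spreads | 91–99% | 72–98% |

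If true frequencies are half the comparator's (comparator total 30 cases, exponent 1), only 38% of the disorders found read as lower.

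**Birth denominator.** Section 3.4 also relates cases to births. The numerator is the same, so the problem remains: about 2 × 71,000 = 142,000 births at 1:100,000 gives 1.42 expected cases for a disorder.

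**Overall and by class.** 30/1,500 = 2.0%, exact 95% CI 1.35–2.84%, far from 9.2%. If the 30 cases fell evenly over three classes (an assumption), 10/1,500 = 0.67%, CI 0.32–1.22%. Against 3.0% the overall comparison is weaker: a one-sided exact 5% test has 75% power at a true 2% and 26% at 2.5%.

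**The case against.** The strongest reply is that the article states no decision rule. It expresses an expectation and says that frequencies will be matched; nowhere does a raw lower value count as confirmation. It is a condensed account, and a test or interval for this comparison may stand in an analysis plan that is not shown. That is right, and the absence of a test is not the point here. A reader might infer that the hypothesis will be judged on the bare sign of each difference; the text does not support that.

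A reader might also infer that chance alone would make more than half of the disorders look lower, or almost none if only those found are compared. Neither holds generally. The share moves from 44% to 79% across all disorders, and from 0% to 58% among those found, with the assumed spread. The hypothesis is aimed at countries where consanguineous marriage is customary, whose rates may be much higher. Against 9.2% (a figure that the article does not label as consanguineous), most of the disorders found would correctly read as lower.

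Other mitigation is real but partial. Section 3.4 already reports totals and class rates, section 2.3.5 speaks of all 37 disorders, and the Discussion admits the limited number of children and calls the study a pilot. The primary outcomes in section 3.1 are metabolite values and the number and proportion of children with abnormal values. The future panel is tied to local frequency and to economic and equipment factors, not to statements about other countries.

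What remains is fixed in the text: the unit of comparison and the restriction to disorders found. No later choice of test gives information to a count of about one.

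**Conclusion.** The point holds in a limited form. On the plan's own figures there are 0.81–1.01 expected cases per disorder, so a comparison for a single disorder is largely uninformative unless the comparator is several-fold higher (about 3.6–4.5 times the average planned rate with no case, 5.5–6.9 times with one). Restricting the comparison to disorders found inflates their frequencies about 1.6–1.8 fold at the average count and 3.9 fold at 0.3 expected cases, against the direction of the hypothesis.

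The expected counts and exact limits need only the planning frequency, the sample size and the number of disorders. The inflation also assumes Poisson counts. No fixed percentage of chance findings should be claimed. The overall comparison is sound against a high comparator and much less so against 3.0%, so the comparator must be named. The change is worth making: it repairs the study's only stated hypothesis using counts that will be collected anyway.

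**What to change.** - In the Introduction, state the hypothesis for the overall detection rate and for the three classes (AAD, OA, FAOD). Name the comparator for each in advance, and call a rate lower only if the upper limit of its exact 95% CI lies below that comparator.
- In task 3 and section 3.4, replace the restriction to identified disorders with all 37, including those with no case, each with an exact 95% CI. Bring the sentence in the Discussion into line. This also agrees with section 2.3.5.
- Describe single-disorder comparisons as descriptive, and call no disorder lower or higher where its CI includes the comparator.

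This needs no more children and no new data, only changed wording and intervals on counts already planned. The price is fewer claims about single disorders.

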## 2 Methods and analysis

### 2.1 Study design and timing

This observational study, uses a cross-sectional design due to its screening nature. The data for the present research will be derived from a selective LC-MS/MS IEM screening of 1,500 clinical-risk children aged 1 day to 18 years and 750 healthy controls of the same age to set reference values for 15 AAs, 35 ACs, and SuAc. The main points of the research are presented in Figure 1 (Flowchart of the study.)

**FIGURE 1 F1:**
[figure not shown]
Flowchart of the study.

The project timing is calculated for 3 years, 2022–2024. The recruitment of healthy children for establishing reference values started on October 2022, and the overall data collection will last until August 2024 (recruitment of high-risk children began in 2023).

### 2.2 Selection of subjects

#### 2.2.1 Sample size estimation

When calculating the sample size for the upcoming project on selective screening, we relied on published similar studies. Researchers pointed out the following essential factors contributing to the sample size calculation: Daniel’s formula for prevalence studies in case of expanded screenings, the reported frequencies of different IEM within the studied populations, and the number of infants born in the country during the period of interest (Yoon et al., 2005; Golbahar et al., 2013; Hassan et al., 2016; Shibata et al., 2018; Sarker et al., 2019; Manta-Vogli et al., 2020). Notably, many researchers corrected their calculations, considering the situation with consanguineous marriages in their country.

According to the review by Shibata N et al., the IEM overall detection frequency was 3.0% (1.2% in Japan and 9.2% in other Asian countries) (Shibata et al., 2018). Yoon et al. reported 5.4% IEM among South Korean annual births (Yoon et al., 2005). Of these data on IEM frequency throughout Asian countries, Mongolian values (1.6%) have attracted our attention due to the similar nomadic history and way of life where consanguineous marriages were strictly forbidden (Shibata et al., 2018). Along with that, the Mongolian index does not include all types of IEM except the most distributed.

Based on mentioned factors, we requested data on the number of childbirths across the four provinces (oblasts) of western Kazakhstan within 3 years before the project started. The average rate of infants born alive annually ranged between 69–73,000 (https://stat.gov.kz/en/industries/social-statistics/demography/publications/). Thus, we have decided to build on the IEM average frequency of 2%–2.5% and determined the expected sample size of 1,500 children for selective screening with 750 healthy controls.

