#### 2.3.4 Diagnosis of targeted diseases (conditions)

The diseases to be analyzed in this study include AAD, OA, and FAOD, which are detected by measuring acylcarnitines, succinylacetone, and amino acids with MS/MS. For their diagnosis, the ratios of Phe/Tyr, C3/Met, C3/C2, C3/C0, С14:1/С2, С14:1/С16, С14:1/С12:1, С0/(С16+С18), and (C14 + C14:1 + C16:1)/C0 will be set. IEMs subject to diagnosis are displayed in Table 3. Limit values will be determined by studying levels of amino acids, acylcarnitines, and succinylacetone in DBSs of 750 healthy children in western Kazakhstan. In the case of normally distributed data, the cut-offs will be set to four standard deviations (SD) above or below the mean. If the distribution of analytes is skewed, reference intervals in the healthy control group will be determined nonparametrically and correspond to the 2.5–97.5th percentile of the experimental distribution. All cut-offs are subject to adjustment in light of further analyzes and additional clinical data.

**TABLE 3 T3:** Primary and repeated LC-MS/MS screening and confirmatory IEM tests.

Disorder	Primary and repeated LC-MS/MS screening	Confirmatory tests
AMINO ACIDS & UREA CYCLE DISORDERS		
PKU	↑Phe, ↑Phe/Tyr ratio	↑Phe, Phe/Tyr ratio (Blood)
		↑Phenyl acetic acid (Urine)
		Genetic sequencing of the PAH gene
MSUD	↑Val, Ile, Leu	↑Val, Ile, Leu (Blood)
	↑ Leu/Ile	↑Val, Leu/Ile, Leu/Phe ratio (Blood)
	↑Leu/Phe	↑α-KG, 2OH-IVA (Urine)
	↑Xle/Ala	Genetic sequencing of the BCKDHA, BCKDHB genes
	↑Xle/Phe	
	↑Val/Phe ratio	
HCU	↑Met, Hcy	↑Met, Hcy (Blood)
	↑Met/phe ratio	
CIT I	↑Cit	↑Cit (Blood)
		↑OA (Urine)
		Genetic sequencing of the ASS1 gene
ASA	↑Argininosuccinic acid	↑Argininosuccinic acid (Blood)
		↑Argininosuccinic acid (Urine)
		Genetic sequencing of the ASL gene
OTCD	↓Cit ↑Orn	↓Cit (Blood)
		↑ Glu (Blood)
		↑Orotic acid (Urine)
		Genetic sequencing of the OTC gene
CPS	↓Cit	↑Organic acids (Urine)
		Genetic sequencing of the CPSI gene
NAGSD	↓Cit	↓Cit (Blood)
		Genetic sequencing of the NAGS gene
TYR I	↑Tyr ↑Tyr/Phe ratio	↑ Cit (Blood)
		↑ SuAc (Urine)
		↑ OA (Urine)
		Genetic sequencing of the FAH gene
TYR II	↑Tyr	Normal levels succinylacetone (Urine)
		Genetic sequencing of the TAT gene
NKHG	↑Gly	↑Gly (Blood)
		↑Gly (CSF/P)
ARG	High arginine ↑Arg/Orn	High plasma arginine and high urinary orotic acid
ORGANIC ACID DISORDERS		
SBCAD	↑С5	Genetic sequencing of the ACADSB gene
MMA	↑C3	↑C3, C3/C2 ratio (Blood)
	↑C3/C2 ratio	↑MMA, 3OH-PA, MCA, PG (Urine)
	↑C4DC, C3/C0	

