### 3.2 Statistical analysis

Shapiro-Wilk and Kolmogorov-Smirnov tests will be used to check the normality of the distribution. As a rule, the distribution of free carnitine and acylcarnitines concentrations in whole blood differs from normal (Manta-Vogli et al., 2020). If the data sets show a normal distribution, M (mean) and standard deviation (error of the mean) will be used for descriptive statistics of the samples. Parametric tests will be used to test for differences between AA and AC concentrations depending on various factors (gender, place of residence) (t-test, analysis of variance (ANOVA) with or without Tukey’s test). If the data sets do not show a normal distribution, Me (median) and quartiles (interquartile range IQR) will be used for the descriptive statistics of the samples. Non-parametric tests (Mann-Whitney U-test, Kruskal-Wallis H-test without or with subsequent *post hoc* comparisons using U-test will be applied to test the differences mentioned above. The Pearson χ^2^ criterion will be applied to identify intergroup differences for categorical variables. If the distribution of analytes is skewed, reference intervals in the healthy control group will be determined nonparametrically and correspond to the 0.5–99.5th percentile of the experimental distribution. Correlations between body weight, and concentration of each analyte will be performed using corresponding tests.

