#### 3.2.1 Descriptive statistics and group comparison

Descriptive statistics and reference intervals for whole blood concentrations of 15 AAs, 35 ACs, and SuAc in healthy children divided into subgroups according to gender will be presented in tables. For each analyte in the healthy control group, the upper cut-off will be set above the 97.5^th^ percentile, while the lower cut-off will be set below the 2.5th percentile. Differences in the distribution of amino acids, acylcarnitines, and succinylacetone between groups, as determined using the Mann-Whitney and Kruskal-Wallis tests, will be noted in the table if found.

Cut-off values for analytes and their ratios for selective screening of AAD, OA, and FAOD presented in Table 3 will be pointed out. The results of determining the analytes in DBS in children of the healthy control group will be compared with those of previously published studies in other populations. According to the inclusion criteria, healthy newborns in the reference group must be full-term (born at 37–42 weeks). However, it should be taken into account that some of the newborns at risk for IEM are born prematurely. In this regard, it is also necessary to determine reference intervals for the concentrations of 15 AAs, 35 ACs and SuAc in dried blood spots of premature infants who do not have clinical symptoms of IEM.

Comparison of mean concentrations (Me, range) of analytes between groups of high-risk children and healthy controls will be presented.

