As such, this study is the first in Kazakhstan and Central Asia to assess the prevalence of IEM among children at risk. Also, reference values of metabolites for three different age groups of the child population in western Kazakhstan will be established for the first time. Our research can be considered a pilot and expected to give an impulse to launch a nationwide ENBS program using LC-MS/MS. Overall, the study will further develop the national as selective as expanded newborn screening programs.

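### The 750 healthy controls are sized from disease frequency, not reference-limit precision; if the 0.5–99.5th percentile rule applies, each age or gender limit rests on one or two children

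*Protocol article*

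**What the plan says.** **Basis of the 750.** Section 2.2.1 (Sample size estimation) lists what similar studies relied on, including "Daniel’s formula for prevalence studies in case of expanded screenings" and reported IEM frequencies. It adds regional births ("The average rate of infants born alive annually ranged between 69–73,000") and then says the authors chose to "build on the IEM average frequency of 2%–2.5% and determined the expected sample size of 1,500 children for selective screening with 750 healthy controls". One basis serves both numbers. No precision, confidence level or subgroup count is given for the controls.

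**Purpose of the 750.** Section 2.3.4: "Limit values will be determined by studying levels of amino acids, acylcarnitines, and succinylacetone in DBSs of 750 healthy children in western Kazakhstan". Reference values are also Task 2 and part of the first primary outcome (Section 3.1).

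**Subgroups.** Section 3.2.1 promises descriptive statistics and intervals "in healthy children divided into subgroups according to gender will be presented in tables". The Introduction makes age-specific intervals from birth to 18 years an objective, and the Discussion says that "reference values of metabolites for three different age groups of the child population in western Kazakhstan will be established for the first time". Section 2.2.2 balances the controls on gender and residence but states no numbers by age.

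**Percentile rule.** For skewed analytes, Section 3.2 says "reference intervals in the healthy control group will be determined nonparametrically and correspond to the 0.5–99.5th percentile of the experimental distribution". For the same case Section 2.3.4 gives the 2.5–97.5th percentile, and Section 3.2.1 sets the cut-offs at the 2.5th and 97.5th. Normally distributed analytes get mean ± 4 SD (Section 2.3.4). Section 3.2 expects free carnitine and the acylcarnitines to be non-normal, so the nonparametric rule would govern much of the panel.

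**The concern.** The precision of a nonparametric reference limit depends on the number of healthy children in the group for which it is set and on how far out the percentile lies. The IEM frequency among suspected children enters neither. The size of the control group was therefore never tested against its task, and no check was made that it suits the percentile rule and the planned subdivision together.

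The at-risk children are read against these limits. A limit fixed by one or two extreme healthy children carries its error into first-tier false positives, into the positive predictive values planned in Sections 3.2 and 3.5, and into reference values that are to be published separately.

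**Working it through.** **1. The plan's own figure.** Daniel's formula is n = z²P(1−P)/d². Section 2.2.1 gives P = 2%–2.5% but no margin d, so neither number can be reproduced from the stated inputs.
- A total of 1,500 follows at 95% confidence if d is assumed to be 0.71 percentage points (P = 2%) to 0.79 points (P = 2.5%).
- With P = 2% and d = 1 point, n = 1.96² × 0.02 × 0.98 / 0.01² = 753, close to 750. That would size a prevalence estimate, not a reference limit. The 750 is also simply half of 1,500.

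**2. Group sizes.**
- Gender: 750/2 = 375 (balance stated in Section 2.2.2).
- Age: 750/3 = 250. Equal groups are an assumption.

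**3. Requirements for a limit at tail proportion p.**
- A rank-based estimate needs (n+1)p ≥ 1. For p = 0.005, n ≥ 1/0.005 − 1 = 199. For p = 0.025, n ≥ 39.
- A 90% equal-tailed nonparametric confidence interval (CI) needs 1 − (1−p)ⁿ ≥ 0.95. For p = 0.005, ln 0.05 / ln 0.995 = 597.6, so 598. For p = 0.025, ln 0.05 / ln 0.975 = 118.3, so 119. With unequal tails allowed, p = 0.005 still needs 460.

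**4. Results under the 0.5–99.5th percentile (Section 3.2).**

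| Group | n | Rank from extreme, (n+1) × 0.005 | Chance no child lies beyond the true limit, 0.995ⁿ | 90% equal-tailed CI |
|---|---|---|---|---|
| All controls | 750 | 3.76 | 2.3% | ranks 1 to 8 |
| Gender | 375 | 1.88 | 15% | none |
| Age, if equal | 250 | 1.26 | 29% | none |

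Reaching 598 per group would take 1,196 children for two genders and 1,794 for three age groups. An age group below 199, which is 26.5% of 750, has no rank-based estimate at all.

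**5. Results under the 2.5–97.5th percentile (Sections 2.3.4 and 3.2.1).** At n = 375 the rank is 376 × 0.025 = 9.4, with 90% CI ranks 5 to 16. At n = 250 the rank is 251 × 0.025 = 6.3, with CI ranks 3 to 12. Both groups exceed 119.

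**6. Direction of the error.** At n = 250 the expected healthy proportion beyond the most extreme value is 1/251 = 0.4%. Interpolating to rank 1.26 gives 1.255/251 = 0.5%, the nominal value. There is no systematic narrowing on average. The spread is the problem: the chance that more than 1% of healthy children lie beyond even the most extreme of 250 values is 0.99²⁵⁰ = 8%.

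**The case against.** **The difficulty depends on one of two conflicting rules.** Only Section 3.2 states 0.5–99.5, and Section 3.2.1, which promises the gender tables, uses 2.5 and 97.5. This stands. Under 2.5–97.5 the 750 is adequate for the promised groups, provided the age groups are not very unequal. But Section 3.2 is current text in the statistics section, and nothing says which rule governs.

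**Limits can still be computed.** A reader might infer that subgroup limits cannot be estimated. The documents do not support that. With 375 or 250 children the 0.5th and 99.5th percentiles fall inside the sample. They fall outside only in an age group under 199, or in crossed age-by-gender cells of about 125, and no section promises crossed cells.

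**The limits are not systematically too narrow.** This stands, as step 6 shows. The fair criticism is imprecision.

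**Consequences are buffered.** Initial cut-offs follow the kit manual (Section 2.3.1), and all may be revised later (Section 2.3.4). Results beyond the limits go to retesting or confirmatory tests (Sections 2.3.1 and 2.3.5). This too stands: final diagnoses are less exposed than first-tier results.

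**An article may leave precision to a fuller plan.** That would excuse silence. Here a basis for the 750 is stated, and it does not bear on the purpose of the group.

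**Conclusion.** The concern holds in a limited form. The 750 has no stated basis in the precision of reference limits. If the 0.5–99.5th percentile of Section 3.2 is applied to skewed analytes by gender or age, each limit rests on the one or two most extreme children. The chance that no child lies beyond the true limit is 15% (n = 375) or 29% (n = 250), and no 90% equal-tailed nonparametric CI can be given. If 2.5–97.5 applies, 750 suffices by gender and by equal age groups.

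The effect falls mainly on first-tier false positives, positive predictive values and the published reference values. Analytes judged normal, which use mean ± 4 SD, are not touched by the rank argument.

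Assumptions: three equal age groups, an even gender split and no samples lost. Uneven ages or exclusions would make the smallest group worse. Age-group sizes do not appear in the text, and the flowchart is not available here.

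**What to change.** - **Sections 2.3.4, 3.2 and 3.2.1:** reconcile the percentile rule. Do not use empirical 0.5–99.5th percentiles in age or gender subgroups; use the 2.5–97.5th by rank there. If 0.5–99.5 is wanted, keep it for the pooled 750, where a 90% interval (ranks 1 to 8) just exists.
- **Reporting:** give a 90% confidence interval with each limit.
- **Section 2.2.1:** replace the IEM-frequency basis for the 750 with the planned number in each age group and the precision it gives.

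**Cost:** wording and a little more analysis, with no extra children. There is a real downside. Per analyte, with both ends flagged, 2.5–97.5 places 5% of healthy children outside the limits against 1% for 0.5–99.5, so more healthy children would be flagged. The stated precision will also look less favourable than a single total of 750 suggests.
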